### 2.1. Objectives and Endpoints

The primary objective for the BLEU clinical trial is to compare healing rates (percent area reduction, PAR) between normal saline wash and an amorphous gel (NSS-HG) to the combination of a synergistic antimicrobial cleanser (AMC) and an antimicrobial gel (AMG) in chronic lower extremity ulcers, including diabetic foot (DFU) and venous leg ulcers (VLU). The primary endpoint is PAR in 4 weeks, with a goal healing rate of 40% in 4 weeks. There is a large body of evidence that supports this rate of healing for DFUs and VLUs [10], and the FDA-sponsored Wound Care Collaborative Community (WCCC) has recommended it as a surrogate endpoint [11].

In addition, an important endpoint in antiseptic clinical trials is a reduction in bacteria. The use of point-of-care fluorescence imaging has simplified this process. Fluorescence imaging will be obtained at every visit and the reduction in bacterial bioburden will be compared between ulcers treated with NSS-HG and AMC-AMG.

Additional secondary endpoints common to most wound-healing clinical trials will be the difference in pain scores and adverse events between subjects treated with NSS-HG and AMC-AMG.

Exploratory endpoints are encouraged if they do not interfere with the primary or secondary endpoints. They contribute to the body of knowledge on chronic wounds and can improve the conduct of future trials. This study will examine host protease levels (matrixmetaloproteases 8 and 9 and neutrophil elastase) using a point-of-care lateral flow test (WOUNDCHEK PROTEASE TEST, WoundChek, Gargrave, UK). In clinical trials, the diagnostic accurately identified wounds with high levels of inflammation. In wounds with a positive test for elevated protease activity (EPA) only 10% were healed at 12 weeks [12].

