### 2.7. Study Procedures

At the screening visit (SV), Day 0, patients will be provided with an informed consent procedure and documentation of the informed consent discussion. The IRB-approved informed consent is obtained prior to performing any trial-related procedures. Once consent is obtained, the physician will document the onset of the ulcer per medical record or patient report, with preference to documentation over self-reporting. The patient’s medical history and demographic information will be recorded. For female patients of childbearing potential, urine or blood pregnancy tests will be conducted. A physical examination will follow and is focused on the integumentary system. Next, a Fitzpatrick score will be assigned. The Fitzpatrick score is a validated assessment of skin tones meant to increase enrollment of minority populations in clinical trials. This is necessary, as an objective assessment of skin color is recommended in all clinical trials, and when using optical diagnostics, the color of the skin is important data.

Due to the inaccuracy of length times width measurements using a hand-held ruler, wound surface area measurement will be assessed using digital planimetry. There are several systems commercially available that accurately measure wound surface area. In this trial, the MolecuLight device in standard photographic mode will provide accurate planimetry. Finally, the patient will complete a baseline pain assessment using a visual analog or numeric scale. Prior or concomitant medications will be reviewed. Quality of life questionnaires will not be used in this trial design due to the short duration of the trial.

This trial design does not incorporate a run-in period such as those used for advanced wound care modalities (e.g., cellular and tissue-based products for wound care (CTP). The goal of antiseptic trials is to identify products that reduce the level of bacteria in the wound; therefore, a run-in to assess healing rate prior to enrollment is unnecessary.

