After the screening visit, enrolled patients will start treatment visit 1. At this treatment visit, initial procedures will be conducted:Confirmation of inclusion criteria and randomization to treatment;Photography of the wound and digital surface area measurement;Fluorescence imaging;Wound cleansing with randomly assigned treatment;Post debridement fluorescence imaging;Swab of wound for protease activity;Application of wound dressing at the discretion of the principle investigator;A four-week supply of the assigned treatment is provided to patients;If applicable, wound debridement, measurement, off-loading walker fitting (DFU applicable), or application of multilayer compression (VLU) is conducted.

At the subsequent treatment visits (visits two through four), all steps will be repeated except for step eight. At the end of the study visit (treatment visit five), final assessments will be conducted to review potential adverse events, concomitant medications, clinical signs and symptoms of infection, and pain status. Pain intensity of the reference ulcer will be assessed before and after any wound cleaning. If applicable, wound debridement, measurement, and photography will be performed. The study exit form will be provided to patients and additional placement of standard-of-care dressings will be provided if the wound has not healed.

Subjects will return weekly for 4 weeks after randomization unless the wound heals, the subject withdraws, or the subject is lost to follow-up.

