A *t*-test will be used to evaluate endpoints concerning mean differences between treatment groups. For the BLEU trial, the t-test will be used to assess the secondary endpoint. The secondary endpoint is to determine the percentage wound area reduction at four weeks. The assumptions of the t-test must be met. These include randomly selected, independent, normal variables that have similar variance. A significance level of 0.05 will be used for this hypothesis test. For these endpoints, the null hypothesis states that the mean difference between the baseline and the end of the study is equal for both treatments, whereas the alternative hypothesis states that the mean between the baseline and the end of the study is not equal for both treatments. Statistical software such as R (version 4.3.1), Excel (version 365), or a TI-83 calculator (TI-83 Plus Graphing Calculator|Texas Instruments) will be used to calculate the test statistics and the *p*-value.

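### Pain is scored at Day 0, but the only rule stated for mean endpoints is an unadjusted t-test of baseline-to-end differences, which leaves that baseline score unused as a covariate

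*Protocol article*

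**What the plan says.** Section 2.1 lists among the secondary endpoints "the difference in pain scores and adverse events between subjects treated with NSS-HG and AMC-AMG".

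Pain is measured at both ends of the study. Section 2.7 says that at screening "the patient will complete a baseline pain assessment using a visual analog or numeric scale". At the last treatment visit, "final assessments will be conducted to review potential adverse events, concomitant medications, clinical signs and symptoms of infection, and pain status", and pain in the reference ulcer is to be rated both before and after cleansing. Table 1 ticks pain at all five visits and labels the instrument PEG.

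Section 2.8 gives the rule for quantitative endpoints: "A *t*-test will be used to evaluate endpoints concerning mean differences between treatment groups". The one endpoint it then names is wound area: "The secondary endpoint is to determine the percentage wound area reduction at four weeks". The hypothesis that follows speaks of endpoints in the plural: "the null hypothesis states that the mean difference between the baseline and the end of the study is equal for both treatments". The level is 0.05 and the alternative is two-sided. Section 2.8 mentions no baseline covariate and no other method for a mean.

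**The concern.** Applied to pain, the stated rule compares mean change scores. A change score gives baseline pain a fixed coefficient of 1, whatever its real relation to final pain. Two things follow.

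- Unless that coefficient happens to be right, baseline noise is carried into the outcome and the confidence interval is wider than the same data allow.
- Randomisation is stratified by site only (section 2.7), so balance in baseline pain is left to chance. The arm that starts higher has more room to regress towards the mean, and the change-score contrast credits this to treatment.

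A model that adjusts for baseline deals with both, using scores already scheduled. What is at stake is the precision of one secondary endpoint in a trial of up to 60 subjects. The article also offers its design as a standard for later antimicrobial trials (Discussion), so the rule may be copied.

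**Working it through.** **Inputs from the article.** 30 per arm, 1:1 allocation, two-sided 0.05. The article gives no pain SD, baseline-to-end correlation (rho), target difference or power for pain. These are assumed below.

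**The plan's own power figure.** Section 2.8 states 80% power with 30 per group for a difference of 0.35. Read as a difference in proportions (chi-square, no continuity correction), power runs from 78.9% to 81.6% for control rates of 0.20 to 0.45. For example, 0.325 against 0.675 gives (0.35×√30 − 1.96×√0.5)/√0.43875 = 0.80, so power is 78.9%. Read as a standardised mean difference, 0.35×√(30/2) − 1.96 = −0.60, so power is only 27%. The 80% therefore belongs to the binary primary endpoint and says nothing about pain.

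**Variance, equal baseline and final SD s.**
- Change score: 2(1 − rho)s²
- Baseline-adjusted (ANCOVA): (1 − rho²)s²
- Ratio: (1 + rho)/2, which is 0.65, 0.75, 0.85 and 0.90 at rho 0.3, 0.5, 0.7 and 0.8

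**Power.** If the change-score test has power P, the adjusted test has power Φ[(z_P + 1.96)/√ratio − 1.96]. For P = 80% and rho 0.5: (0.842 + 1.960)/√0.75 − 1.96 = 1.275, giving 89.9%. Gains in percentage points:

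| Assumed power of change-score test | rho 0.3 | rho 0.5 | rho 0.7 | rho 0.8 |
|---|---|---|---|---|
| 30% | 12.9 | 8.1 | 4.4 | 2.8 |
| 50% | 18.1 | 11.9 | 6.6 | 4.2 |
| 70% | 16.9 | 11.8 | 6.9 | 4.5 |
| 80% | 13.5 | 9.9 | 6.0 | 4.0 |
| 90% | 8.0 | 6.3 | 4.0 | 2.7 |

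A noncentral-t check at 30 per arm (58 against 57 df), with a true effect of 0.5 SD of raw pain, gives gains of 15.1, 11.6, 6.9 and 3.4 points at the same four correlations. For a large effect with high rho, where the change-score test is already near certain, little is left to gain: 0.1 point at 0.8 SD and rho 0.8.

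**Unequal SDs.** With k = final SD / baseline SD, the ratio is k²(1 − rho²)/(1 + k² − 2·rho·k). At k = 1.3:
- rho 0.5: 1.69×0.75/1.39 = 0.91
- rho 0.7: 1.69×0.51/0.87 = 0.99

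From 80% starting power these give about 83.5% and 80.4%, gains of 3.5 and 0.4 points. The ratio reaches 1 when rho×k = 1.

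**Chance imbalance.** The standard error of the baseline difference is √(2/30) = 0.26 SD. With equal SDs, an imbalance of one standard error shifts the change-score contrast by (1 − rho)×0.26 SD: 0.18, 0.13 and 0.08 SD at rho 0.3, 0.5 and 0.7, towards the arm that starts with more pain.

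**The case against.** The strongest objection is that the article never says how pain will be analysed. Section 2.8 attaches the t-test by name to percentage area reduction alone, and details for a minor secondary endpoint may sit in an analysis plan that is not shown. This stands in part: pain reaches the t-test only through the general opening sentence and the plural in the null hypothesis. But the rule is stated in general terms, pain scores compared between arms fit it, and nothing else is offered. The point is about a stated method, not a missing detail.

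A reader might infer that the t-test costs about 10 points of power. The document does not support that figure. It needs rho near 0.5, equal SDs and 80% power for pain, none of which is given, and the article's 80% is for the primary endpoint.

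A reader might also infer that the t-test is biased. Under 1:1 randomisation it is not, and its type I error is sound. The shift exists only given a chance imbalance in baseline pain.

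It is also fair to say that the pain measure is unsettled: two descriptions of the instrument, readings before and after cleansing, and weekly visits that may stop when the wound heals. This makes any assumed correlation less certain and has to be settled for any pain analysis, adjusted or not.

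**Conclusion.** The point holds as a modest improvement to a secondary endpoint, not as an error that threatens the trial. The stated rule is valid but leaves out a covariate that is already collected. In large samples the adjusted analysis is never less efficient than the change-score or the raw-score t-test, so the direction of the advantage does not depend on the assumed rho. Its size does. With equal SDs it is roughly 3 to 18 points for rho 0.3 to 0.8 and starting powers of 30% to 90%. It is close to nothing if final pain is sufficiently more variable than baseline pain (k = 1.3 with rho 0.7) or if power is already near 100%. The protection against chance baseline imbalance needs no assumption about power.

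**What to change.** In section 2.8, add one sentence for pain: the main analysis is a linear model of end-of-study pain on treatment arm and Day 0 pre-cleansing pain, reported as the adjusted mean difference with its 95% confidence interval. The t-test can stay as an unadjusted summary.

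Both scores must be on the same scale. First reconcile section 2.7, which allows either a visual analogue or a numeric rating, with the PEG entry in Table 1. State also which final-visit reading is used, since section 2.7 takes one before and one after cleansing. If the analysis plan already adjusts for baseline pain, align the published rule with it.

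The model costs one degree of freedom and needs no extra visits, measurements or subjects.

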### 2.9. Subject Withdrawal

All subjects have the right to withdraw at any point during treatment without prejudice. Whether each subject completed the clinical study will be documented. If, for any subject, study treatment or observations are discontinued, the reason(s) will be recorded. The investigator can discontinue a subject at any time if it is considered medically necessary. The termination of study participation is not anticipated to affect subject safety. If a subject withdraws consent to participate in the study or is withdrawn by the investigator, attempts must be made to obtain permission to record at least survival data up to the protocol-described end of the subject follow-up period. Reasons for withdrawal or early termination will be obtained whenever possible.

A subject will be considered lost to follow-up if they cannot be contacted after 5 phone calls and 3 letters.

### 2.10. Subject Compensation

Patients will be compensated USD 35 after completion of each study visit. This is a nominal compensation that offsets the cost of travel, parking, and the additional time required to collect information specific to the study.

### 2.11. Anticipated Risks/Risk Mitigation

Anticipated risks associated with the study procedures are listed below, along with the applicable risk mitigation. Adverse events related to the treatment are unlikely. The potential risks are listed in Table 2.

## 3. Discussion

Chronic wounds are a growing public health problem [17]. A new medical specialty has arisen to meet the needs of millions of patients suffering from this disabling condition. As with any new specialty, well-conducted research into treatment regimens and diagnostics has lagged. The field of wound care needs standardized endpoints and clinical trial design. The Wound Care Collaborative Community was established by the United States Food and Drug Administration (FDA) in 2021. The goal of the organization is to standardize clinical trial endpoints, design, and technologies. In the past, the FDA only recognized complete wound healing as an approved endpoint for wound care clinical trials [11,12]. The WCCC has recognized that complete closure is not always the appropriate endpoint for wound care technologies [12]. For example, complete wound closure is not an appropriate endpoint for topical antiseptics that are designed to reduce bacterial burden and prepare the wound for technologies that facilitate complete closure. The WCCC has suggested several surrogate endpoints, such as a percent surface area reduction of 40% in four weeks [12]. The primary endpoint for the protocol described here employs this surrogate endpoint.

It is necessary to use double blinding for clinical trials involving antimicrobial agents. The benefits of double blinding in clinical research include detection of causality between the treatment and wound healing, reproducibility of the study, and bias reduction.

The BLEU protocol design incorporates the recognized surrogate endpoint of 40% PAR at 4 weeks. It is also important in antimicrobial trials to assess the reduction in bacterial levels. This is accomplished using fluorescence imaging, a point-of-care-validated device that eliminates the need for the invasive and costly biopsies needed for quantitative cultures. Unlike most wound-healing clinical trials, this design utilizes double blinding, which reduces bias.

The primary source of evidence for the use of antimicrobial cleansers and gels is lab and preclinical. The lack of clinical trials in the wound care population leaves many clinicians confused as to how and when to use topical antimicrobials for chronic wounds. There is also little guidance on the choice of antimicrobials. Utilizing the trial design described here will standardize clinical trials evaluating the efficacy of topical antimicrobials. It will also allow for comparative effectiveness studies between antimicrobials.

## 4. Conclusions

The BLEU clinical trial design to evaluate topical antimicrobials incorporates an accepted surrogate endpoint and assesses bacterial reduction in a blinded fashion. This trial design allows for the evaluation of topical antimicrobials in the chronic wound population.

## Figures and Tables

**Table 1 life-13-01983-t001:** Schedule of events.

	SV, TV 1	TV 2	TV 3	TV 4	TV 5/EOS
Window Period	Day 0	Day 7	Day 14	Day 21	Day 28
Informed consent	√				
Documentation of onset of wound	√				
Medical history and demographics	√				
Physical exam	√				
Urine or blood pregnancy test (females of childbearing potential)	√				
Infection status	√	√	√	√	√
Assessment of pain status—PEG	√	√	√	√	√
Prior and concomitant medication review	√	√	√	√	√
Wound cleansing	√	√	√	√	√
Wound measurements/photographs	√	√	√	√	√
Adverse event review		√	√	√	√
MolecuLightTM photos (2)	√	√	√	√	√
WoundChekTM protease test	√				√

**Table 2 life-13-01983-t002:** Anticipated risks.

Study Procedure	Anticipated Risks	Risk Mitigation
Wound cleansing	Pain, bleeding, allergic reaction (e.g., rash).	Procedures to be performed by trained clinical staff
Wound measurements	None anticipated	N/A
Pain assessments	None anticipated	N/A
Wound photos	None anticipated	N/A
BIAKOS™ Antimicrobial Skin & Wound Cleanser	Allergic reaction	Procedures to be performed by trained clinical staff
BIAKŌS Antimicrobial Wound Gel	Allergic reaction	Procedures to be performed by trained clinical staff
Dressing placement	None anticipated	N/A

## Data Availability

The data is proprietary, but is available on request to the corresponding author.
